## Abstract

**Background:**

Low back pain (LBP) is a major public health problem. Risk factors for the development and persistence of LBP include physical and psychological factors. However, most research activity has focused on physical solutions including manipulation, exercise training and activity promotion.

**Methods/Design:**

This randomised controlled trial will establish the clinical and cost-effectiveness of a group programme, based on cognitive behavioural principles, for the management of sub-acute and chronic LBP in primary care. Our primary outcomes are disease specific measures of pain and function. Secondary outcomes include back beliefs, generic health related quality of life and resource use. All outcomes are measured over 12 months. Participants randomised to the intervention arm are invited to attend up to six weekly sessions each of 90 minutes; each group has 6–8 participants. A parallel qualitative study will aid the evaluation of the intervention.

**Discussion:**

In this paper we describe the rationale and design of a randomised evaluation of a group based cognitive behavioural intervention for low back pain.

## Background

Low back pain (LBP) is a major public health problem [1,2]. In the UK, the annual period prevalence of LBP is approximately 37% [3,4]. A study conducted in the UK found that 75% of people with LBP who consulted their general practitioner (GP) still had symptoms one year later; 30% had developed persistent disabling LBP [5,6]. The direct health care costs associated with LBP in 1998 were £1628 million; the majority of this was spent on physiotherapy and general practice [1].

Since the early 1990s there has been a change in the emphasis of LBP treatment with strong discouragement of bed rest and encouragement of physical activity becoming an orthodox approach. This active management strategy forms the core of all international guidelines for the management of acute (< 3 months) LBP [7-12]. Less attention has been paid to the management of chronic low back pain. The active management approach is sometimes supplemented with patient education materials. In the UK, 'The Back Book' is advocated [13,14]. Evidence to support other physical treatments is weak [15]. A recent UK study found no difference between six sessions of physical therapy and a single session of active management supplemented by 'The Back Book' [16] There are no recommendations relating to the use of psychologically based treatments [17].

A number of studies indicate that cognitive behavioural approaches (CBA) may be beneficial in the management of sub-acute and chronic LBP [17-22]. However, none of the trials to date has been of sufficient size or duration to determine long-term clinical and there has been little attention paid to the cost effectiveness of CBA.

Applications of CBA for LBP have varied in content and method of delivery [23]. In the UK, the first applications of CBA were in-patient pain management programmes for very chronic low back pain. CBA appears moderately effective in this context [18], but the effect on people presenting in general practice, often with less severe symptoms, is unknown. Although not formally reported, pain management programmes are expensive because of the intensity of intervention and high staff costs. Less expensive CBA, such as short group programmes led by a nurse or therapist, would appear highly applicable to general practice, but have not been widely implemented or studied in such settings. Potential advantages include; preventing chronic disability, increasing physical and psychosocial functioning in patients with disability due to low back pain, and decreasing inappropriate health care utilisation. In other chronic conditions the social interactions and comparisons that occur in a group-based intervention have been identified as potentially important mediators of the therapeutic effect [24]. The Back Skills Training Trial (BeST) has been designed to capture and evaluate these effects using a combination of qualitative and quantitative methodologies.

There is a need to establish if group based CBA is an effective approach in the management of sub-acute and chronic LBP, and if baseline characteristics are important predictors of treatment response. We will determine the effectiveness of adding a group based, professionally led CBA for LBP to active management in general practice on

• LBP related pain and disability

• time lost from occupational activity

• fear avoidance beliefs

• the use of further medical, rehabilitation, surgical or alternative treatments for LBP

• generic health related quality of life

• health service costs.

The target population are individuals with low back pain of at least moderate troublesomeness and of at least six weeks duration. The effects will be monitored over a 12-month period. Evaluation will include an appropriate method of cost appraisal which will consider both the health and societal perspective.

## Methods/Design

### Setting

Around 98% of the UK population is registered with a general practitioner. We are recruiting participants from 97 general practices, with a total list size of 700,000 patients in seven localities (Primary Care Trusts) across England; South Warwickshire, North Warwickshire, Coventry, Solihull, North Norfolk, Southern Norfolk, Norwich, Broadland, Langbaugh, Heart of Birmingham, and South Birmingham. The population in these localities is broadly representative of the population of England. Participants from practices in each locality are able to attend the same treatment centre ensuring sufficient numbers to sustain the group sessions without making participant travel burdensome.

### Ethical approval

West Midlands Multi-Centred Research Ethics Committee, Birmingham UK (MRC/03/7/04) provided the ethical review and approval.

### Study Population

Potential participants who have consulted their general practice with back pain in the last six months are identified by searching the practice computerised medical record or are identified by practice clinical staff when they attend the practice. They are sent an invitation letter and eligibility questionnaire by post. Those people who indicate a willingness to participate, and fulfil the first stage eligibility criteria are invited to an initial interview with a research nurse at which there are further eligibility checks, and potential participants are provided with a detailed explanation of the study purpose and procedures. At a second appointment, at least one week later, informed consent is obtained, baseline data are collected, the participant is randomised and the 'active management approach' to managing back pain is reinforced. This includes providing all participants with a copy of 'The Back Book'.

### Eligibility criteria

Inclusion criteria are LBP of at least moderate troublesomeness and of at least six weeks duration; age greater than 18 years; willing and able to give informed consent and to understand/speak English. People are ineligible if they have been managed previously in a cognitive behavioural programme; have "Red Flags" i.e. factors associated with serious LBP pathology (including cauda equina symptoms, systemic illness (including cancer, HIV, fever); widespread neurological problems, severe unremitting night-time pain, violent trauma (fall from height, RTA), unexplained weight loss); or have severe psychiatric or personality disorders. There is consensus that CBA and related interventions are unnecessarily intensive for people who suffer an isolated acute or minor episode of LBP, in whom symptoms resolve quickly and pose no on-going problem [25]. We are seeking to recruit participants with at least moderately troublesome sub-acute or chronic low back pain [26]. Measuring 'troublesomeness'/'bothersomeness' is a simple criterion for determining overall symptom burden [27,28].

### Baseline Assessment

Data are collected using a standard pro forma administered by a specially trained research nurse. These include age, gender, ethnicity, educational attainment, general health status, duration of LBP, symptoms, recent treatment history, anxiety and depression (using the Hospital Anxiety and Depression Scale [29]) and employment status. In addition participants complete the baseline (pre-intervention) versions of the outcome measure package (see Table 1).

**Table 1 T1:** Outcomes measures

	Domain	Measures	Time points (months)
Primary	Pain & Disability	Roland & Morris Questionnaire (Roland 1983)	0, 3, 6, 12
	Pain	Von Korff Scale (Von Korff 1992)	0, 3, 6, 12
Secondary	Occupational and other limitations	Numbers of days off work, reduced activity and bed rest	0, 3, 6, 12
	Health related quality of life inc physical & mental health	Short Form 12 version 2 (Ware 1996)	0, 3, 6, 12
	Back Pain Beliefs	Fear avoidance scale (1^st ^five items only)* (Waddell 1993)	0, 3, 6, 12
	Self-efficacy	Pain self-efficacy questionnaire (Nicholas 2006)	0, 3, 6, 12
	Satisfaction with treatment	Single item rating of satisfaction with treatment (Deyo et al 1998)	12
Economic analysis	Resource Use	Resource use questionnaire	6, 12
	Health related quality of life; time trade off score	EQ-5D (health utility) (EuroQol Group 1990)	0, 6, 12

### Treatment allocation

Following completion of the baseline assessment, the research nurse completes a randomisation form and telephones a central randomisation office to obtain the treatment allocation. A minimisation algorithm is used to ensure that, within each treatment arm, near equal numbers of participants are entered from each centre within the differing levels of troublesome back pain (moderately or very/extremely troublesome). The nurse provides the advice component of the intervention to all study participants, and for participants randomised to CBA, sends a notification letter to the local service provider. The service provider then contacts the participant to arrange a day/time to start the CBA treatment. Fig 1

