### Other treatments

All participants receive a simple active management intervention including a copy of 'The Back Book' [13]. The important components of the active management strategy are emphasised by the research nurse; namely,

• Encouragement to remain active and resist bed rest.

• Advice on appropriate methods of pain control.

Before starting the study the research nurses are trained in delivery of the active management strategy supplemented by 'The Back Book' [13]. Participants are asked to act on the guidance. Participants can if they wish seek further assistance from their GP or chosen back care provider. GPs are able to refer patients to any other services that they consider appropriate.

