### Sample size

The sample size has been estimated using well-documented methods [36], with careful consideration of the practicalities to ensure that sufficient numbers of participants are randomised within an acceptable time frame. We originally planned a 1:1 randomisation ratio between CBA and usual care. Early in the trial we recognised that a 2:1 randomisation (in favour of CBA) had distinct advantages in ensuring that sufficient numbers of patients are randomised to sustain the group sessions. A randomisation balance of 2:1 can be adopted with inconsequential loss of power, but further imbalances necessitate an increase in study size. From a list size of 100,000 (approximating to one location), with twice as many participants being randomised to the intervention group, we estimated the yield of participants randomised to the group sessions was 1.4 per week, allowing us to recruit eight participants to a new group starting every six weeks. This estimate was based on data from the UK BEAM trial [37].

The potential impact of the group effect was also considered in the sample size estimation. In this trial, other effects include the individual practitioner treating several groups, regions and organisations. We perceive that the most potent of the cluster effects is the group effect, and is the only effect to have been considered formally in the sample size estimation (using methods described by [38]).

The sample size target for the trial is 700 to detect a moderate effect size, and a difference between the groups of approximately 1.8 RDQ points, assuming a standard deviation of 4.27 points (giving an effect size of 0.42). Approximately 233 participants will be randomised to active management alone and 467 participants on the active management + CBA arm of the trial. The sample size has been inflated to account for an inter-cluster correlation co-efficient of 0.01 (based on UK – BEAM [37] and incorporates a loss to follow up of 25%. We have used a power of 90% and p < 0.01 [39]. Effect sizes of approximately 0.4 are considered to be clinically worthwhile for back pain interventions [23]. The sample size requirement will be reviewed by an independent data monitoring committee at approximately the mid point of data accumulation.

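### As described, the nurse learns the allocation before giving the advice common to both arms, which leaves an avoidable route for unequal delivery

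*Protocol article*

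**What the plan says.** The Study Population section of the protocol article lists the steps of the second appointment: consent, baseline data, randomisation, then advice. In its words, "the participant is randomised and the 'active management approach' to managing back pain is reinforced".

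The Treatment allocation section says that, after baseline assessment, the research nurse completes a form and "telephones a central randomisation office to obtain the treatment allocation". It continues: "The nurse provides the advice component of the intervention to all study participants". The same sentence adds that, for participants allocated to CBA, the nurse sends a notification letter to the local provider.

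The Other treatments section describes the advice. "All participants receive a simple active management intervention including a copy of 'The Back Book", and "The important components of the active management strategy are emphasised by the research nurse". It names two components: staying active rather than resting in bed, and suitable methods of pain control. It also states a safeguard: "Before starting the study the research nurses are trained in delivery of the active management strategy". Participants in either arm may seek further help from their GP or another provider.

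The Sample size section defines the control arm: "Approximately 233 participants will be randomised to active management alone". About 467 participants receive active management plus CBA.

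**The concern.** The Background section sets the question as the effect of adding group CBA to active management. That contrast is clean only if active management is delivered alike in both arms. If the person giving the advice already knows the arm, there is an obvious reason to say more to someone who will get nothing further from the trial, or less to someone about to start six 90-minute group sessions. The opposite is also possible: a nurse may convey disappointment, or show less interest, to a control participant.

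Either pattern would enter the between-arm difference. The primary outcomes (Roland and Morris questionnaire, Von Korff scale) are completed by participants. Analysis by intention to treat keeps people in their randomised arm but does not correct for a base treatment delivered differently in the two arms.

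**Working it through.** The plan gives no figure on this point, so the main check is a reading of the sections together.

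**Order of events**

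| Question | Study Population | Treatment allocation | Other treatments |
|---|---|---|---|
| When is the arm obtained? | After consent and baseline data | After baseline, by the nurse's telephone call | – |
| When is the advice given? | Listed after randomisation | Stated after the call, in the sentence that also covers the CBA notification letter | Timing not stated |
| Who gives it? | – | The nurse | The research nurse, verbally, with the booklet |

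1. Two sections independently list allocation before advice, and no section gives the reverse order.
2. The person who makes the call is the person who gives the advice, so the nurse's knowledge of the arm follows from the text. The participant's knowledge at that moment is an inference, and the point does not need it.
3. The notification letter can only be sent once the arm is known. Placing the advice in the same sentence fits advice after allocation.
4. Everyone receives the advice, so nothing in it depends on knowing the arm. The order could be reversed without changing what is delivered.

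**How sensitive the comparison would be to a shift (hypothetical)**

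Inputs from the Sample size section: SD 4.27, target difference 1.8, arms of 233 and 467, 25% loss, intra-cluster correlation 0.01, significance level 0.01. The upper group size of 8 is from the Experimental intervention section. Assumptions: two-sided test (the article does not say), normal approximation, clustering in the CBA arm only, and the plan's SD. The main analysis uses area under the curve, whose SD is not given.

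- Design effect = 1 + (8 − 1) × 0.01 = 1.07.
- Followed up: 0.75 × 233 = 174.75 and 0.75 × 467 = 350.25.
- SE = 4.27 × √(1/174.75 + 1.07/350.25) = 0.40 points.

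Let b be the shift in the between-arm difference from unequal advice. The document gives no value for b, so the column below is an assumption over a range.

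| Assumed b (points) | Type I error at nominal 0.01, no true effect | Power at 0.01 if the shift runs against CBA and the true difference is 1.8 |
|---|---|---|
| 0 | 0.010 | 97% |
| 0.25 | 0.026 | 90% |
| 0.5 | 0.092 | 75% |
| 1.0 | 0.47 | 28% |

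The top of the range is more than half the target difference, which is a great deal to expect from variation in one advice session. The table shows only how the comparison would respond to a shift. It is no evidence that one exists. The 97% at b = 0 is above the plan's stated 90%; nothing here depends on that gap.

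**The case against.** **The order is read from narrative.** The Treatment allocation sentence does not say when the advice is given, and the Study Population sentence joins its items with a plain conjunction. Reinforcing an approach may imply that it was introduced earlier. The flow diagram was not available in the text reviewed. This stands as a reason to write 'as described'. It does not reverse the reading: two sections agree, and even an approach introduced earlier would be reinforced by a nurse who knows the arm.

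**Delivery is already standardised in part.** Nurses are trained before the study, the key components are fixed, the intervention is simple and the booklet is the same for all. This stands, and it lowers the risk. A reader might infer from the lack of a script or fidelity check that delivery is loose. The article does not support that, because such detail commonly sits in the full protocol or a manual.

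**The advice is not all the care that controls receive.** This is correct. They may consult their GP or another provider, so the advice and booklet are the whole of what the trial supplies, not the whole comparator experience.

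**The effect is small beside the unavoidable lack of blinding.** Participants cannot be blinded to group sessions, and moving the call leaves that in place. This also stands. It limits what the change achieves, but it is no reason to keep an avoidable source of difference.

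**Conclusion.** The point holds as a modest design weakness. As the article describes the second appointment, the nurse knows the arm while giving advice that is intended to be common to both arms. Training, fixed components and the booklet reduce the risk of unequal verbal delivery but do not remove it.

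Two stronger readings are not supported. A reader might infer that the comparison is biased, or that a set share of the 1.8-point target is lost: assumed shifts of 0.2 and 0.4 points would be 0.2/1.8 = 11% and 0.4/1.8 = 22%. Those percentages only divide a guess by the target. A reader might also infer that any bias must work against CBA. More effort with controls, or less with the CBA arm, would dilute the effect; the reverse would inflate it. The document settles neither size nor direction.

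The conclusion rests on the order in the text being the order in practice. The case for acting is that the correction costs almost nothing while recruitment is open.

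**What to change.** For the remaining recruitment, make the telephone call to the randomisation office the last step of the second appointment. The sequence would be consent, baseline data, the common advice and booklet, then the call. The content of the advice stays as it is. Amend the Study Population and Treatment allocation text to match, and record the date on which each centre changes.

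If practice already follows this sequence, only the wording needs correcting.

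**Cost.** A one-line change to the nurse procedure, with no extra visit, staff or data. Minimisation is unaffected, because centre and troublesomeness are known before the call.

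**Downside.** Recruitment has begun and is due to close in March 2007, so participants already randomised will have followed the present order and the trial will contain a mixed procedure. Results before and after the change can be set out by date, but order is not randomised in that comparison. It would be descriptive only and could not establish whether the present order caused bias.

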**Figure 1 F1:**
[figure not shown]
Flow diagram of the study

### Experimental intervention

Back Skills Training is a 'complex' intervention, comprising a number of components that may act both independently and inter-dependently [30]. The components are;

(i) education to counter unhelpful beliefs about LBP and to highlight the importance of appropriate levels of activity;

(ii) use of cognitive re-structuring techniques to counter unhelpful beliefs;

(iii) training on goal setting, baseline setting, and pacing for incrementally increasing activities;

(iv) specific focus on fear avoidance and attentional effects on pain;

(v) techniques for self-management of pain especially in flare-ups.

These components are delivered using a cognitive behavioural model and focus on group problem solving to increase self-efficacy. The treatment sessions are delivered to groups of approximately 6–8 patients, using six weekly sessions of 90 minutes length each. The rationale and the components will be described in detail elsewhere. A participant is deemed to have received the intervention if they attend the baseline assessment, and three of the six follow-up sessions. Therapists and nurses receive a one and half day training programme including basic principles of the cognitive behavioural approach, questioning, facilitation of groups, pacing, coping, relaxation, exercise, and pain management. Training and support are provided by a qualified cognitive behavioural therapist and physiotherapist. The intervention is structured around standardised sessions and supplemented by a participant workbook.

### Other treatments

All participants receive a simple active management intervention including a copy of 'The Back Book' [13]. The important components of the active management strategy are emphasised by the research nurse; namely,

• Encouragement to remain active and resist bed rest.

• Advice on appropriate methods of pain control.

Before starting the study the research nurses are trained in delivery of the active management strategy supplemented by 'The Back Book' [13]. Participants are asked to act on the guidance. Participants can if they wish seek further assistance from their GP or chosen back care provider. GPs are able to refer patients to any other services that they consider appropriate.

